### Outcomes

The two primary outcomes for the study are informed choice and decisional conflict. Informed choice will be measured by the percentage of women in each arm of the trial identified as making an informed choice using the MMIC [11]. Decisional conflict will be measured by the difference in mean scores of the Decisional Conflict Scale [15] between women in each arm. Both primary outcomes will be measured based on data from the first questionnaire to reflect women's experience closest to the time they were making decisions about prenatal testing.

Secondary outcomes include attitudes to the pregnancy/fetus, depression, anxiety, and acceptability of the written information by women and GPs. These outcomes will be measured using data from the first questionnaire. Women's satisfaction with their decision [37] will be assessed using data from the second questionnaire.

Changes in primary and secondary outcomes will be measured by comparing responses from the second questionnaire with the first. Attitudes to the pregnancy/fetus will be assessed using the scale developed by Reading et al (1984) [34] by measuring the difference in mean scores between women in both arms of the trial. Depression will be measured using the difference in percentages of women in both arms of the trial identified as being probably clinically depressed on the EPDS [35]. Anxiety will be measured as the difference in the mean Anxiety STAI-State (short version) score of women in both arms of the trial [36]. The acceptability of the decision aid/pamphlet to women and GPs will be measured by comparing the difference in proportions of descriptive items between women in both arms of the trial and comparing content analysis of open-ended comments.

Satisfaction with decision making will be measured using the difference in mean Satisfaction with Decision Scale [37] scores between women in both arms of the trial.

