### Setting for the trial

The ADEPT study is being conducted in the primary health care setting of Victoria, one of the south-eastern states of Australia, where approximately 62,000 women give birth each year [20]. All women in Victoria booked to give birth at a publicly funded maternity setting have access to a second trimester maternal serum screening test, free of charge. Within this public system, women identified as being at 'increased risk' for fetal abnormality on the basis of their age (37 years or older) or screening test result, have access to diagnostic testing that is fully funded. Outside these criteria women incur out-of-pocket expenses for most other screening or diagnostic tests, although some costs are covered by a federally funded rebate. All serum samples are sent to a centralised laboratory at GHSV for testing.

In Victoria, the provision of information on prenatal testing options is not uniform. Some women receive information that is verbal and/or written, while others receive no information at all. The pamphlet produced by the GHSV is one of a vast array of written information used throughout the state. While the exact rate of uptake of screening tests in the state is not known, it is estimated that approximately 60% of pregnant women have some form of screening test [21] and utilisation is increasing. An abnormal screening test result was the indication for 44% of diagnostic tests in 2004, compared to 41% for maternal age alone [22].

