### Data collection from women

Women were asked to complete two questionnaires, the first by 14 weeks gestation and the second at approximately 24 weeks gestation. The initial questionnaire was given to the woman by her GP and the second questionnaire was forwarded to her postal address by the project team. Stamped addressed envelopes have been provided for the return of both questionnaires.

Once written informed consent was obtained from the woman by her GP, an enrolment form detailing the date, woman's name, contact details and estimated due date was faxed to the study office. This information was entered into a database to manage the reminder system for the questionnaires as well as the mail-out of the second questionnaire.

Using a modification of the technique described by Dillman [32], a two-stage reminder system is in place to maximise the response rate of the questionnaires. Women are contacted with a reminder letter two weeks after the questionnaire is due if it has not been received. A phone call reminder follows in a further two weeks if the questionnaire remains unreturned.

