### Scales

ADEPT is using validated and psychometrically robust self-report scales.

The Multi-dimensional Measure of Informed Choice (MMIC) [11] scale defines an informed choice as one that is based on relevant knowledge, is consistent with a person's values and is behaviourally implemented. Three dimensions are incorporated in this measure: knowledge, attitude and uptake. There are eight knowledge items and four items on attitudes to screening tests. A record of test uptake is included in the measure. Dichotomous outcomes are classified as informed choice or uninformed choice. The classification of an informed choice is determined by a score higher than the midpoint of the knowledge scale (>4), higher than the midpoint of the attitude scale (>12) and having the test. Equally, a choice is classified as informed when a score is higher than the midpoint of the knowledge scale (>4), less than the midpoint of the attitude scale (equal or <12) and not having the test [33].

The Decisional Conflict Scale [15] contains 16 items divided into three sub-scales: uncertainty about selection of alternatives; specific factors contributing to uncertainty and perceived effectiveness of decision-making. Respondents use a five-point Likert scale (1 = strongly agree to 5 = strongly disagree). The mean scores are reported for the total scale and each sub-scale. Higher scores indicate higher decisional conflict.

The Attitudes to the Fetus/Neonate [34] measure consists of 15 adjectives and respondents use a seven point scale (0 = Not at all to 7 = extremely) to describe their feelings in relation to being pregnant (nine items) and towards the fetus (six items). By reversing specific items the mean scores are calculated for attitudes to pregnancy and the fetus, with higher scores indicating a more positive attitude.

The Edinburgh Postnatal Depression Scale [35] has been validated to use prenatally. It contains ten items and respondents have four options available to indicate the frequency of the event based on their experience of the previous week. With the reversing of specific responses, items are scored (1–4) and women can be classified as probably clinically depressed (≥ 13) or not (<13).

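### Informed choice requires actual test uptake, but uptake is taken from a questionnaire due by 14 weeks, before most second-trimester tests are likely to have happened

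*Protocol article*

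**What the plan says.** Under Scales, the informed-choice measure is described thus: "Three dimensions are incorporated in this measure: knowledge, attitude and uptake". On uptake, the section adds: "A record of test uptake is included in the measure". A woman who scores above the knowledge midpoint is informed in one of two ways. Either her attitude score is "higher than the midpoint of the attitude scale (>12) and having the test", or it is "less than the midpoint of the attitude scale (equal or <12) and not having the test".

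Under Outcomes, the data source is fixed: "Both primary outcomes will be measured based on data from the first questionnaire". The reason given is that this is nearest in time to the decision. The same section plans to compare the second questionnaire with the first for changes in the primary outcomes.

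Under Data collection from women, two questionnaires are scheduled, "the first by 14 weeks gestation and the second at approximately 24 weeks gestation". Late forms are chased: "Women are contacted with a reminder letter two weeks after the questionnaire is due if it has not been received". A telephone call follows two weeks after the letter. Women enter the trial at 12 weeks or earlier (Inclusion criteria for women).

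Under Setting for the trial, women booked at publicly funded maternity services "have access to a second trimester maternal serum screening test, free of charge". The Background gives as a reason for working in general practice that women are reached early enough to weigh options in both trimesters.

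**The concern.** The outcome needs a completed behaviour, but its data source closes before part of that behaviour is likely to have taken place. Knowledge, attitude and decisional conflict are best measured near the decision. Uptake is not, because a second-trimester test may be chosen at 12 weeks and done some weeks later.

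The error runs in both directions. A well-informed woman waiting for the test she wants is moved from informed to uninformed. A well-informed woman who did not favour testing but is tested later is left as informed when the completed behaviour would make her uninformed.

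Informed choice is the outcome on which the trial was powered. Misclassification that is equal in both arms shrinks the difference. Misclassification that differs by arm, for example through a shift between first- and second-trimester tests or in return times, could create or hide a difference. The planned change from first to second questionnaire would also partly record tests done in between.

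**Working it through.** **1. The plan's own sample size.** For 50% versus 68%, two-sided 0.05 and 80% power, the pooled-variance formula with continuity correction gives 127 women per arm. Then 127 × 1.25 = 158.75, so 159, and 159 / 0.65 = 244.6, so 245. Both stated figures reproduce. The sample-size arithmetic is not at fault; the problem is when uptake is observed.

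**2. What the rule does to a pending test** (knowledge score above 4 throughout):

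| Attitude | Status at questionnaire 1 | Scored | After later test |
|---|---|---|---|
| >12 | test chosen, not yet had | uninformed | informed |
| ≤12 | not tested, later tested | informed | uninformed |

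No section says that uptake for the primary outcome comes from another source, or how a chosen but pending test is scored.

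**3. Illustrative size.** The inputs below are assumptions, except where the protocol is named.
- Attitudes: 60% positive, 10% neutral, 30% negative. Neutral women are treated as non-positive, as the rule does for a score of 12.
- Uptake by attitude: 85%, 50% and 15%. Overall: 0.6 × 0.85 + 0.1 × 0.50 + 0.3 × 0.15 = 60.5%, in line with the roughly 60% in Setting for the trial.
- f = share of tests not yet done when the first questionnaire is completed, equal in both arms.
- The planned 50% and 68% are taken as rates under completed uptake.

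Among knowledgeable women, the share scored informed is

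c(f) = 0.6 × 0.85(1 − f) + 0.1 × [1 − 0.50(1 − f)] + 0.3 × [1 − 0.15(1 − f)].

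c(0) = 0.51 + 0.05 + 0.255 = 0.815. Observed rate = true rate × c(f) / 0.815.

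Power = Φ[(d − 1.96 × SE₀) / SE₁], where d is the observed difference, SE₀ the pooled and SE₁ the unpooled standard error, without continuity correction. With 159 / 25 = 6.36 women per GP, the design effect is 1 + 5.36 × 0.05 = 1.268, and effective n per arm = 159 / 1.268 = 125.4. (The plan's 1.25 corresponds to 6 women per GP.)

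| f | c(f) | Observed rates | Difference (points) | Power |
|---|---|---|---|---|
| 0 | 0.815 | 50.0% vs 68.0% | 18.0 | 0.83 |
| 10% | 0.7735 | 47.5% vs 64.5% | 17.1 | 0.78 |
| 20% | 0.732 | 44.9% vs 61.1% | 16.2 | 0.73 |
| 40% | 0.649 | 39.8% vs 54.2% | 14.3 | 0.62 |

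**4. A second, simpler set of assumptions.** Suppose 60% of informed choices are informed by having a test, a share s of those tests is missed, and errors in the other direction are ignored. The observed rate is the true rate × (1 − 0.6s). With design effect 1.25, power is 0.84 at s = 0, 0.78 at 10%, 0.69 at 25% and 0.53 at 50%. The pattern is the same.

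**5. Timing that differs by arm, no true effect.** If 70% of women in both arms are knowledgeable and 30% versus 50% of tests are missed, the observed rates are 0.7 × 0.6905 = 48.3% and 0.7 × 0.6075 = 42.5%. This is a false difference of 5.8 points. Its sign depends on which arm has the later tests.

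**The case against.** Several stronger readings are tempting, and the protocol does not support them.

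- *No second-trimester test can be captured.* The gestational window of the test is not given. With reminders at two and four weeks after the due date, some forms will come back at about 16 to 18 weeks or later, when some tests may already be done. This limits the number missed, but it also makes recorded uptake depend on return date.
- *A large share of women is misclassified.* The 60% uptake figure is not split by trimester. First-trimester samples were reaching the central laboratory in 2004 (Enrolling GPs in the ADEPT study), so early screening was in use.
- *Pending tests are certainly coded as no test.* The questionnaire item is not shown and could record booked or intended tests. What stands is that the stated rule turns on having the test and mentions no intention.
- *The arms will differ in test timing.* No section says that the decision aid shifts women between trimesters or changes return times. That bias is possible, not shown.

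The planned 50% and 68% may also not refer to completed uptake, since the difference was based on a study of knowledge. And using the first questionnaire was a deliberate choice with a stated reason. That reason is sound for knowledge, attitude and decisional conflict. It does not extend to behaviour that has yet to occur. Nor is this a detail left to a fuller document: the article itself fixes both the scoring rule and the data source.

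**Conclusion.** The concern holds for the uptake component of one primary outcome. As written, the scoring rule and the data source together misclassify women whose chosen test is still pending when they complete the first questionnaire. Decisional conflict does not use uptake and is unaffected.

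The direction of the problem follows from the text; its size does not. A loss of about 1 to 4 points from the 18-point difference, with power of 0.78 to 0.62 against 0.83, rests on assumed attitude shares, assumed uptake by attitude and an assumed 10% to 40% of tests missed equally in both arms. The false difference of about 6 points rests on an assumed imbalance in timing. These figures show that the matter is worth settling before analysis; they do not estimate what will happen in this trial.

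**What to change.** Keep knowledge and attitude from the first questionnaire, and take the uptake component of the primary informed-choice outcome from the 24-week questionnaire. State a rule for women who do not return it: for example, use first-questionnaire uptake, with a chosen but pending test scored by a rule written down in advance. Report the version based only on the first questionnaire as a sensitivity analysis. If change in informed choice between questionnaires is reported, say that it partly reflects tests done in between. Because the researchers are not blinded, the definition should be fixed before outcomes are compared by arm.

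The cost is a short change to the outcome definition. The second questionnaire is already planned, and comparing primary outcomes across the two already calls for uptake at 24 weeks. The downside is loss at the second questionnaire, since the 35% allowance covers only first-trimester miscarriage and non-return of the first. If women without it were dropped, a further 15% loss leaves 135.15 per arm (design effect 1.2203, effective n 110.8) and power 0.78. A 25% loss leaves 119.25 (1.1885, 100.3) and power 0.74. Falling back on first-questionnaire uptake limits this loss, at the price of some remaining misclassification in those women.

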## Discussion

Standard guidelines for statistical reporting of clinical trials will be followed [38] with additional information relating to the cluster design [31,39,40]. Baseline characteristics of women including age group, marital status, educational level, income source, country of birth, religion will be compared between the intervention and control arms of the trial. In addition, obstetric history, previous experience with prenatal screening tests, perception of risk of Down syndrome and personal experience with individuals who have disabilities such as Down syndrome will be compared between arms of the trial. GPs will be compared between arms in relation to age, gender, country of graduation, years of general practice, postgraduate education and personal and professional experience with individuals who have disabilities like Down syndrome. In addition we will compare GPs in both arms of the trial on the basis of the average time spent informing women of prenatal tests and the importance they attach both to providing this information and to women having prenatal testing.

Differences in the primary outcomes will be analysed using 'intention-to-treat' principles. The primary outcome of informed choice is binary and analysis will use logistic regression to evaluate the difference in proportions between the two arms of the trial. Linear regression will be used for the other primary outcome, decisional conflict, to evaluate the difference in mean scores between the two arms of the trial. Adjustment will be made for the stratification variable, geographical location (metropolitan/rural), and the following major potential confounding factors: maternal age, education level, gravidity, socioeconomic status and country of birth. Confidence intervals and P values will be adjusted for the effect of clustering and loss to follow-up within clusters will be reported.

Secondary outcomes will use appropriate regression techniques and covariate adjustments.
